#### Preliminary Efficacy Outcomes

To prepare for a fully powered trial, we will examine recommended primary and secondary outcomes for the efficacy of the intervention [67-69]. The primary preliminary efficacy outcomes are the number of days of cannabis use, the number of times of cannabis use, and the negative consequences of cannabis use. Days of cannabis use are consistently associated with clinical outcomes, and evidence to date supports the use of this measure to determine cannabis reduction in clinical trials [70]. The number of self-reported days of cannabis use in the past 30 days will be assessed via a TLFB calendar at baseline, 3 months, and 6 months; cannabis use days in the past 14 days will be assessed via TLFB at 3 weeks. For each day with cannabis use, participants will be asked to estimate the time(s) of cannabis use and report their certainty about the time(s) to capture information about changes in total cannabis exposure [70]. The number of self-reported negative consequences of cannabis use in the past 3 months will be measured on the 19-item (yes or no) Marijuana Problems Scale at baseline, 3 months, and 6 months [71].

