We will preliminarily examine the efficacy of MOMENT-V on 30-day cannabis use frequency and on past 3-month negative consequences or problems with cannabis use at 3 and 6 months. To control for potential confounders identified in bivariate analyses of group differences at baseline, we will regress follow-up outcomes on treatment status, adjusting for baseline measures in intention-to-treat analyses. We will conduct analyses using generalized linear mixed-effects models. Models will include the study participant as a random effect and fixed effects for the study arm and potential confounders and covariates such as sociodemographic factors. We will conduct both intention-to-treat and per-protocol analyses to evaluate the robustness of the findings.

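### The cannabis-use model covers only 3 and 6 months and gives the 3-week use days no role, so it cannot account for dropout related to early use; adding them is a cheap, minor improvement

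*Protocol article*

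**What the plan says.** **Collection (protocol article, Preliminary Efficacy Outcomes).** Days of cannabis use is one of the primary preliminary efficacy outcomes. "The number of self-reported days of cannabis use in the past 30 days will be assessed via a TLFB calendar at baseline, 3 months" and again at 6 months. In addition, "cannabis use days in the past 14 days will be assessed via TLFB at 3 weeks". Negative consequences are recorded on the "Marijuana Problems Scale at baseline, 3 months, and 6 months", so that scale has no 3-week value.

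**Analysis (protocol article, Quantitative Data).** The use outcome is fixed as follows: "We will preliminarily examine the efficacy of MOMENT-V on 30-day cannabis use frequency". The same sentence ends with "negative consequences or problems with cannabis use at 3 and 6 months". The model form is "we will regress follow-up outcomes on treatment status, adjusting for baseline measures in intention-to-treat analyses", fitted as a generalized linear mixed model: "Models will include the study participant as a random effect and fixed effects for the study arm and potential confounders and covariates". Intention-to-treat and per-protocol versions are both planned. The 3-week use days are not mentioned.

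**The concern.** With baseline as a covariate, only 3- and 6-month values are outcome rows. Someone who attends the 3-week visit and then leaves for good has no row, and the participant random effect cannot bring in a person without rows. Their post-randomization use has been measured but is set aside.

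A likelihood-based mixed model accounts for dropout only as far as dropout depends on what is in the model. Here that is arm, covariates including baseline, and any later value observed. If return at 3 months depends on use just after the intervention, the variable carrying that information is left out. This is plausible: the Randomization section leaves participants and research assistants unmasked, the Conditions section gives the two arms very different amounts of contact, and Strengths and Limitations accepts that lack of blinding may affect retention. At stake is the preliminary 3- and 6-month effect on use days, which is examined to prepare for a fully powered trial.

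**Working it through.** **1. The article's own figure.** Sample Size gives 80% retention at 3 months in 60 participants, to within ±10 points. Check: 1.96 × √(0.80 × 0.20 / 60) = 0.101. It reproduces.

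**2. How many can be lost from the model.** Number without a 3-month value = 60 × (1 − retention).

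| Retention at 3 months | With a 3-month value | Without |
|---|---|---|
| 90% (upper limit of the stated interval) | 54 | 6 |
| 80% (stated expectation) | 48 | 12 |
| 70% (lower limit of the stated interval) | 42 | 18 |

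Twelve is an upper bound at 80% for the group in question. Anyone who misses 3 months but attends 6 months keeps a row. Anyone who leaves before the 3-week visit has no 3-week value to add.

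**3. Bias with no true effect, 3-month comparison.** Assumed, not in the documents: SD 9 days; correlations 0.6 (baseline with 3 weeks), 0.7 (3 weeks with 3 months) and 0.5 (baseline with 3 months); about 20% dropout; 30 per arm; 8000 simulated trials per scenario. Dropout depends on 3-week use in MOMENT-V only and is random in EUC.

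| Log-odds of dropout per SD of 3-week use | Mean estimate without / with 3-week value (days) | SD without / with |
|---|---|---|
| 0.7 | −0.43 / 0.01 | 2.26 / 2.19 |
| 1.0 | −0.64 / 0.01 | 2.30 / 2.23 |

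The negative sign is a spurious benefit, because heavier users leave the MOMENT-V arm. Relative to the SD of the estimate, the bias is 0.43/2.26 = 0.19 and 0.64/2.30 = 0.28. The SD falls by 0.07/2.26 = 3.1% and 0.07/2.30 = 3.0%.

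**4. Dependence on the dropout pattern.** A rerun with both the 3- and 6-month outcomes in the model (SD 9, similar correlations, about 20% dropout) gave these biases at 3 months:

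| Dropout related to 3-week use | Bias without 3-week value (days) | With it |
|---|---|---|
| One arm only | about −0.5 to −0.8 | about 0 |
| Both arms, unequally | about −0.3 | about 0 |
| Both arms, equally | about 0 | about 0 |
| Not at all (random) | about 0 | about 0 |

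The SD fell by 2-4%.

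**5. A second set of assumptions.** True effect −3.0 days, SD 8, correlations 0.5-0.6, a random-intercept model averaged over 3 and 6 months, 300 runs. With one-arm dependence the mean estimate was −3.51 without the 3-week value and −3.11 with it. With equal dependence it was −2.89 and −3.01. Simulation error is about 1.7/√300 = 0.10, so only the −3.51 is clearly away from −3.0. The model without the 3-week value used 50-51 of 60 participants on average; the model with it used all 60, since everyone was assumed to reach 3 weeks.

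**6. Limits of these checks.** All simulations treated use as a continuous score on one scale. They did not model a bounded count over 14 or 30 days, so they show direction and rough size only.

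**The case against.** **The analysis plan may deal with this.** The article is a condensed account and does not rule out imputation or auxiliary variables. That stands: the absence of a missing-data method here is no fault. What the article does fix is the outcome, the visits and the place of baseline, and that choice omits a collected measurement. The phrase about follow-up outcomes could be stretched to include 3 weeks, which the Outcomes section lists as a follow-up. But the sentence before it names 30-day use at 3 and 6 months, and a 14-day count is not that.

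**The intention-to-treat label.** A reader might infer that the label is contradicted. It is not. The article sets it against per-protocol, the ordinary sense of analysis by assigned arm, and a baseline-adjusted mixed model of follow-up values is routinely so called.

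**Bias is not established.** A reader might infer that the estimate will be biased. The documents give no evidence that dropout relates to early use differently by arm, and without such a difference the bias is about 0. This stands in full.

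**The 3-week value is awkward.** The EMI starts the day after the one-week session and runs 14 days, so the 3-week window nearly coincides with active self-monitoring in one arm. Restricting the efficacy contrasts to 3 and 6 months is therefore defensible. That argues against 3 weeks as an endpoint, not against using it to inform the later contrasts.

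**Modelling baseline as an outcome to keep everyone in.** This looks attractive but adds almost nothing on the arm contrast for people with baseline data only. It also gives essentially the same answer as baseline adjustment for the Marijuana Problems Scale.

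**Conclusion.** The point holds as a minor improvement. As described, the model ignores 3-week use days, loses at most 12 of 60 participants at 80% retention, and cannot account for dropout related to early use. Under the assumed inputs the consequence is about 0.3 to 0.8 days per 30 if that dropout differs by arm, and about 0 otherwise. Against an SD of the estimate near 2.3 days, even 0.8 is 0.8/2.3, or about a third of a standard error.

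The precision gain is also modest. Observing all 60 instead of 48 would cut the SD by 1 − √(48/60) = 10.6%; the 3-week value recovers about 2-4%. It would be wrong to read the fix as restoring the full sample.

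The loss of up to 12 rests on the article's own retention figure. The bias and precision figures rest on assumed SDs, correlations and dropout slopes. The primary outcomes are feasibility measures, and no power is claimed for use days.

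**What to change.** For cannabis use days, add the 3-week TLFB value to the mixed model. Suggested text:

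> Use days at 3 weeks, 3 months and 6 months will enter as repeated outcomes, each as days used out of days assessed (14, 30 and 30), with a participant random effect and fixed effects for arm, visit, arm-by-visit and baseline use. The reported estimates are the arm contrasts at 3 and 6 months, expressed as days per 30. The 3-week value is supporting information.

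The arm-by-visit terms are essential. With the single arm effect now listed, the 3-week rows would mix use during the EMI into the later contrasts.

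The cost is a slightly more complex model, using data already being collected. The gain is confined to participants who reach the 3-week visit. The intention-to-treat wording and the Marijuana Problems Scale analysis need no change.

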#### Qualitative Data

We will examine the domains addressed in the 6-month interview via immersion/crystallization [85], template organizing style [86], and thematic analysis [87] approaches. First, we will use immersion/crystallization to familiarize ourselves with the data by reading a subset of transcripts and creating memos about potential codes and themes [85]. Then a codebook will be developed using a template organizing style with inductive and deductive codes and tested on the same subset of transcripts used for immersion/crystallization [86]. The codebook will be used to code the full set of interview transcripts using the online mixed methods program Dedoose (SocioCultural Research Consultants, LLC). After completing initial coding of all transcripts, we will apply a “code cleaning” process to determine if each code captures a distinct idea, during which some codes will be combined and others will be split into new codes. Finally, themes will be developed using a thematic analysis approach [87], in which data will be consolidated into major themes and subthemes by creating groups of codes that are thematically related. Coding discrepancies and thematic disagreements will be resolved through ongoing discussion and consensus among the coding team. Survey data will be used descriptively to contextualize the interview data.

## Results

We began enrolling participants in August 2025. We anticipate completing enrollment in January 2027 and data collection in July 2027. We will report on the primary outcomes by the first half of 2028, including on ClinicalTrials.gov, where the trial protocol and statistical plan can also be accessed. We will follow NIH data sharing policies to make a deidentified dataset readily available. We intend to present the findings from this study at national scientific meetings and through publications in journals pertaining to adolescent health, substance use, public health, mental and behavioral health, or related fields. In collaboration with the study’s Advisory Board, we will develop and implement plans to disseminate the findings to participants who have elected to receive this information, and to general patient populations, clinicians, and administrators of the recruitment clinics.

## Discussion

### Anticipated Findings

Using mixed methods and a pilot randomized trial design, this study will provide evidence of the feasibility and preliminary efficacy of the MOMENT-V telehealth-plus-EMI intervention to reduce cannabis use among young adults with CUD who are seen in primary care settings. The study will also provide evidence of the feasibility of the remote trial procedures in anticipation of a future fully powered efficacy trial of the MOMENT-V intervention vs EUC.

### Strengths and Limitations

The MOMENT-V intervention has been developed based on a solid conceptual framework, best practices for behavior change counseling, empirical data, and young adult input. This study will use recommended methods to evaluate feasibility; we will collect data on multiple validated and standardized measures and compare the results with a priori benchmarks. Data will be collected electronically, and rigorous procedures to monitor counselor fidelity and ensure data quality will be used. A pilot test of MOMENT-V provided preliminary evidence that young adults with CUD engaged with the intervention and found it helpful [53].

This study may be limited by challenges with recruitment and retention owing to factors outside our control, such as clinic or participant disengagement or competing demands. We will make every effort to support successful recruitment by using inclusive, prominently displayed recruitment materials, developed with input from young adult and community advisors, and by maintaining ongoing communication with clinic staff regarding recruitment and study progress. The research team will meet weekly to review enrollment and promptly identify and address issues. We will mitigate attrition by implementing a detailed informed consent process, offering respectful remuneration, collecting extensive locating information, maintaining frequent contact, and using appealing methods, in addition to conducting all study activities remotely. To further support study engagement, we will invite participant feedback on surveys and in an interview. We will optimize intervention completion and EMI engagement by scheduling MET sessions and report prompts around work/school schedules and sleep hours and by sending text reminders about participation. Participants will not be blinded to their study condition, which may influence their satisfaction ratings, retention, and other outcomes. Because participation is voluntary, the results may not be generalizable to young adults with CUD who are not seeking treatment or not motivated to participate in research.

### Conclusions

The growing public health crisis of CUD [88] in young adults mandates the availability of evidence-based, developmentally appropriate, accessible, affordable, and practical treatment that will be acceptable to patients and clinicians alike. By combining telehealth MET with mHealth EMI, the innovative and scalable MOMENT-V offers a brief fully remote approach for implementation within primary care, addressing many treatment barriers for the vulnerable and underserved population of young adults with CUD. Should the MOMENT-V intervention and procedures prove feasible in this rigorous randomized pilot trial, a large trial will be warranted to evaluate the intervention’s efficacy and advance much-needed research on CUD treatment for young adults.
